### Exclusion criteria

Compromised health, primary teeth with more than one third root loss, lack of internal pathological resorption, impossibility of restoration, cases of re-treatment and crypt involvement.

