### Inclusion criteria

Children aged 3 to 6 years, with at least 1 primary anterior tooth with irreversible pulpitis or pulp necrosis due to caries or trauma suitable for restoration, and at least two thirds of the root remaining; otherwise health patients who have not been submitted to antibiotic therapy in the previous 3 months.

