### Clinical and radiographic evaluations of teeth

The clinical evaluations will be performed with the child in a dental chair under the light of the reflector, with the aid of a mouth mirror and palpation of the area around the affected tooth. During the initial exam as well as the follow-up exams at 1, 3 and 6 months after endodontic treatment, the following clinical data will be recorded: history of spontaneous pain indicative of apical periodontitis, presence of fistula or abscess, gingival swelling and pathological tooth mobility. The radiographic exams will involve the evaluation of signs of radiolucency in the periapical region and pathological root reabsorption.

The data collected during the initial exam as well as the follow-up exams at 1, 3 and 6 months after endodontic treatment and the comparison of the initial diagnostic radiographic exam to the radiographic exams at 1, 3 and 6 months after treatment will constitute the basis for the evaluation of the treatment success or failure. The radiographs will be analyzed by two experienced examiners with the aid of a negative viewing box (negatoscope). These examiners will not receive any information regarding the type of treatment each tooth received. Cases of divergence will be resolved by consensus between the two examiners [17].

The following criteria will be used for the determination of treatment success or failure:Complete repair (= success)Clinically: absence of signs and symptoms;

Radiographically: absence of pathological root resorption, normal width of periodontal ligament space, absence of lesion development in periapical regions in cases of absence of lesion in the initial diagnostic radiograph and complete regression of lesion in cases of presence of lesion in the initial diagnostic radiograph.2.Incomplete repair (= success)Clinically: absence of signs and symptoms;

Radiographically: absence of pathological root resorption and reduction lesion size in the periapical region.3.Lack of repair (= failure)Clinically: signs and symptoms indicative of acute apical periodontitis;

Radiographically: presence of pathological root resorption, lesion in furcation/periapical region unchanged in size during follow-up period, increase in lesion size or the development of a new lesion [17].

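### One exclusion criterion appears inverted: as worded, only teeth with internal pathological resorption are eligible, and such teeth could hardly meet either success grade

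*Protocol article*

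**What the plan says.** The Exclusion criteria begin with compromised health and continue: "primary teeth with more than one third root loss, lack of internal pathological resorption, impossibility of restoration, cases of re-treatment and crypt involvement". The item at issue is "lack of internal pathological resorption". The Inclusion criteria address the root only through its remaining length: "suitable for restoration, and at least two thirds of the root remaining". They do not mention internal resorption.

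Under Clinical and radiographic evaluations of teeth, the radiographic examination covers "evaluation of signs of radiolucency in the periapical region and pathological root reabsorption". Three grades follow:

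- Complete repair, a success, requires "absence of pathological root resorption, normal width of periodontal ligament space", together with conditions on lesions.
- Incomplete repair, also a success, requires "absence of pathological root resorption and reduction lesion size in the periapical region".
- Lack of repair, the failure grade, lists "presence of pathological root resorption, lesion in furcation/periapical region unchanged in size during follow-up period", lesion growth or a new lesion, next to a clinical element.

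**The concern.** An exclusion list names features that keep a tooth out. Here one item keeps a tooth out because an adverse feature is missing. Taken at its word, it turns away teeth without internal pathological resorption and admits only teeth that have it.

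That affects two things. The first is the study population, because this is the only eligibility rule on internal resorption in the article. The second is the success outcome, because both success grades require that pathological root resorption be absent. A trial whose stated aim is clinical and radiographic evaluation would then be grading teeth that enter with a sign barring them from success.

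**Working it through.** No arithmetic decides this point, and the article gives no figure to reproduce. The check sets the passages side by side.

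1. **Direction of the list items.** The other exclusions are compromised health, root loss beyond one third, a tooth that cannot be restored, re-treatment and crypt involvement. All are adverse. Only the resorption item excludes the absence of an adverse feature.

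2. **Literal eligibility.** Excluded means that internal pathological resorption is lacking. Eligible therefore means that it is present. On this reading the rule applies to all 30 planned teeth, 15 per group.

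3. **Correction elsewhere.** The Inclusion criteria cover age, pulp status, cause, restorability, remaining root, general health and recent antibiotics. None of these bears on internal resorption, so nothing there overrides or repairs the exclusion.

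4. **Link to the outcome (assumption).** The grades speak of pathological root resorption and define no subtypes. I take internal pathological resorption to fall under that term. This is the natural reading, but it is an inference.

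5. **Consequence for the grades.**

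| Grade | Condition on resorption | Literally eligible tooth, resorption persisting |
|---|---|---|
| Complete repair (success) | must be absent | not met |
| Incomplete repair (success) | must be absent | not met |
| Lack of repair (failure) | presence is a listed sign | radiographic sign met |

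A success would require the resorption to be no longer present at 1, 3 or 6 months. If it persists in both arms, neither arm records a success and the comparison carries no information.

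6. **Reach of the problem.** The sample size (Subjects) and the named between-group tests (Data organization and statistical analysis) rest on bacterial counts and their percentage reduction. Those analyses do not use the success grades, so they could still be computed. They would, however, describe the population that the same criterion selects.

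**The case against.** The strongest reply is that this is plainly a slip of the pen. The article contains many language errors, the neighbouring items show what was probably meant, and nothing in it shows that staff screen by the literal text. I accept that, and it rules out any claim that the wrong teeth have been enrolled. It does not remove the need for a correction. An eligibility criterion is an operative rule: if it is followed, the population changes; if it is quietly ignored, each enrolled tooth without resorption departs from the written criteria.

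Several stronger readings are tempting, and the article does not support them:

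- *The two rules contradict each other.* An eligibility rule and an outcome rule can both be applied. The literal result is a success grade that is nearly out of reach, not a logical impossibility.
- *Every tooth would be a failure at baseline.* The failure grade has a clinical and a radiographic element, and the article does not say whether either suffices alone. A symptom-free tooth with persisting resorption misses both success grades but is not clearly a failure.
- *Resorption is never compared with the baseline film.* The evaluation section states in general terms that success or failure rests on comparing the initial and follow-up radiographs. The grade definitions apply change over time explicitly only to lesions, but the general rule is there.
- *The whole trial loses its ability to compare the arms.* The bacterial-count analyses do not depend on the grades.

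It might also be said that an article condenses a fuller protocol. That excuses an omission, but this criterion is stated, and it appears to be stated the wrong way round.

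**Conclusion.** The point stands as an apparently inverted eligibility criterion that fits badly with the success grades. Its size is conditional. If the wording is followed literally, and if internal resorption counts as pathological root resorption, none of the 30 teeth could reach either success grade while the resorption persists, and the success outcome named in the aim could hardly separate the arms. If, as seems likely, the wording is a drafting error that screening does not follow, the outcome is unaffected and what remains is a misdescribed population. The article does not show which of these applies. Because the rule governs who enters the trial, it should be corrected in either case.

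**What to change.** The investigators should reconcile the Exclusion criteria with the success grades under Clinical and radiographic evaluations of teeth, and state the exclusion in the direction they intend. If they mean to exclude teeth with internal pathological resorption, deleting the words *lack of* is enough. Which eligibility rule is clinically appropriate is for them to decide.

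Trial status reports that recruitment began in September 2015 and is planned to run to December 2015. Teeth already screened or enrolled should therefore be checked against the corrected wording, and any that do not fit should be reported.

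The cost is one wording correction by amendment and a review of the screening records for at most a few months of recruitment. The grades themselves, which the article takes from a cited source, need no rescoring of resorption for this purpose.

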### Experimental groups

#### Randomization

The type of treatment will be randomly determined for each tooth using tiles on which 1 of 2 numbers is printed (Table 1):

**Table 1 Tab1:** Experimental groups

Experimental groups	
Group I (*n* = 15)	Conventional endodontic treatment
Group II (*n* = 15)	Endodontic treatment with administration of PDT

*PDT* photodynamic therapy

Number 1: conventional treatment (Group I).Number 2: treatment with PDT (Group II).

### Blinding procedures

The clinical and radiographic evaluations of endodontic treatment will be performed by examiners who will be blinded to the allocation of the teeth to the different groups.

### Clinical and radiographic evaluations of teeth

The clinical evaluations will be performed with the child in a dental chair under the light of the reflector, with the aid of a mouth mirror and palpation of the area around the affected tooth. During the initial exam as well as the follow-up exams at 1, 3 and 6 months after endodontic treatment, the following clinical data will be recorded: history of spontaneous pain indicative of apical periodontitis, presence of fistula or abscess, gingival swelling and pathological tooth mobility. The radiographic exams will involve the evaluation of signs of radiolucency in the periapical region and pathological root reabsorption.

The data collected during the initial exam as well as the follow-up exams at 1, 3 and 6 months after endodontic treatment and the comparison of the initial diagnostic radiographic exam to the radiographic exams at 1, 3 and 6 months after treatment will constitute the basis for the evaluation of the treatment success or failure. The radiographs will be analyzed by two experienced examiners with the aid of a negative viewing box (negatoscope). These examiners will not receive any information regarding the type of treatment each tooth received. Cases of divergence will be resolved by consensus between the two examiners [17].

The following criteria will be used for the determination of treatment success or failure:Complete repair (= success)Clinically: absence of signs and symptoms;

Radiographically: absence of pathological root resorption, normal width of periodontal ligament space, absence of lesion development in periapical regions in cases of absence of lesion in the initial diagnostic radiograph and complete regression of lesion in cases of presence of lesion in the initial diagnostic radiograph.2.Incomplete repair (= success)Clinically: absence of signs and symptoms;

Radiographically: absence of pathological root resorption and reduction lesion size in the periapical region.3.Lack of repair (= failure)Clinically: signs and symptoms indicative of acute apical periodontitis;

Radiographically: presence of pathological root resorption, lesion in furcation/periapical region unchanged in size during follow-up period, increase in lesion size or the development of a new lesion [17].

All radiographs will be standardized and taken with minimal geometric distortion, which is achieved using adult periapical film (Kodak, Rochester, NY, USA) in the occlusal position and a radiographic positioner for the child in the vertical direction (modified occlusal radiograph). This procedure will allow the same position of the film at the different evaluation times and standardize the incidence of X-rays, vertical and horizontal angles and distance on all radiographs taken for the same patient [17].

The same development time, intermediate washing, fixation and final washing at all evaluation times will be used to standardize the radiograph processing. Room temperature (camara escura) will also be standardized and Kodak chemicals (Kodak, Rochester, NY, USA) will be used. Radiographic exposure time, kilovolts and milliamps of the device as well as the type of film will be standardized to obtain the most identical density and contrast possible among the radiographs [17].

### Administration of PDT

The Therapy XT-EC (DMC ABC Medical and Dental Equipment, São Carlos, SP, Brazil) will be used for PDT, with laser emission in the red band (660 nm) and the narrow tip for the specific use of PDT in areas of difficult access (Figs. 1, 2). During administration, only the volunteer and operator will be present and both will wear eye protection. The active tip of the laser will be wrapped in disposable transparent plastic wrap (polyvinyl chloride, PVC) for reasons of hygiene and the avoidance of cross-contamination. The operator will be duly vested.

**Fig. 1 Fig1:**
[figure not shown]
Laser Therapy XT-EC

**Fig. 2 Fig2:**
[figure not shown]
Full width at half maximum (FWHM) spectral width (nm)

One session of PDT with the Chimiolux® methylene blue photosensitizer (Hypofarma, Belo Horizonte, MG, Brazil) at a concentration of 0.005 % will be performed in the interior of the root canal. The photosensitizer will be applied with a sterile paper cone for 3 minutes and the excess will be removed with an endodontic aspirator. The canal will be irradiated for 40 seconds, with the device previously calibrated to emit a wavelength at 660 nm, with radiant energy of 4 J and mean maximum power of 100 mW (Table 2). The direct contact method will be employed, based on a previous study [4, 7].

**Table 2 Tab2:** Lasers parameters

Parameters	Red laser
Central wave length (nm)	659.93 nm
FWHM spectral width (nm)	0.82
Operating mode	Continuous
Mean maximum power (mW)	100
Polarization	Random
Aperture diameter (cm)	0.060
Radiance at aperture (mW/cm^2^)	38197
Beam profile	Multi-mode
Beam area (cm^2^)	1
Radiance at target (mW/cm^2^)	108
Exposure time (s)	40
Radiant exposure (J/cm^2^)	4.3
Radiant energy (J)	4.32
Number of irradiated points	1
Irradiated area (cm^2^)	1
Application technique	Contact
Number of sessions	1
Total radiant energy (J)	4.32

*FWHM* Full Widht Hay Maximum

### Interventions

All treatment procedures will be performed by a single, duly-trained operator.

### Group I (control) – conventional endodontic treatment

Prophylaxis with pumice stone and water and antisepsis of region with 0.12 % solution of chlorhexidine using moistened gauze.Anesthesia.Absolute isolation, if possible; in cases of considerable loss of remaining tooth, relative isolation using cotton rolls.Opening of crown with spherical diamond tip burs (bur size compatible with tooth) (KG Sorensen – Indústria e Comércio, Cotia, SP, Brazil) and high-speed Z endodontic drill under water and air refrigeration.Millimeter measurement of root canal to 1 mm short of radiographic apex.Insertion of 3 sterile paper cones with diameter compatible with canal for 30 seconds for initial collection of bacterial sample and immediate placement into brain heart infusion broth.Surgical chemical preparation with series of Kerr files appropriate for each case, using an initial file and an additional 2 files of larger size, with irrigation and aspiration with 1 % sodium hypochlorite (Milton’s solution) and Endo-PTC (Fórmula e Ação, São Paulo, SP, Brazil) with each change of file.Insertion of 3 sterile paper cones for 30 seconds for second collection of bacterial sample and immediate placement into brain heart infusion broth.Filling of root canals with calcium hydroxide (UltraCal, Ultradent, Indaiatuba, SP, Brazil); base of thin *gutta-percha* and filling with glass ionomer cement; restorative treatment performed in subsequent session.

### Group II – conventional endodontic treatment + PDT

Prophylaxis with pumice stone and water and antisepsis of region with 0.12 % solution of chlorhexidine using moistened gauze.Anesthesia.Absolute isolation, if possible; in cases of considerable loss of remaining tooth, relative isolation using cotton rolls.Opening of crown with spherical diamond tip burs (bur size compatible with tooth) (KG Sorensen – Indústria e Comércio, Cotia, SP, Brazil) and high-speed Z endodontic drill under water and air refrigeration.Millimeter measurement of root canal to 1 mm short of radiographic apex.Insertion of 3 sterile paper cones with diameter compatible with canal for 30 seconds for initial collection of bacterial sample and immediate placement into brain heart infusion broth.Surgical chemical preparation with series of Kerr files appropriate for each case, using initial file and an additional 2 files of larger size, with irrigation and aspiration with 1 % sodium hypochlorite (Milton’s solution) and Endo-PTC (Fórmula e Ação, São Paulo, SP, Brazil) with each change of file.Insertion of sterile paper cone immersed in Chimiolux® methylene blue (Hypofarma, Belo Horizonte, MG, Brazil) for 3 minutes; administration of wireless Therapy XT- EC laser device (DMC ABC Medical and Dental Equipment, São Carlos, SP, Brazil) after removal of cone; energy density: 4 J/cm^2^, power: 100 mW; wavelength: 660 nm; exposure time: 40 seconds.Root canal irrigated with sterile saline solution and insertion of 3 sterile paper cones for 30 seconds for second collection of bacterial sample and immediate placement in brain heart infusion broth.Filling of root canals with calcium hydroxide (UltraCal, Ultradent, Indaiatuba, SP, Brazil); base of thin *gutta-percha* and filling with glass ionomer cement; restorative treatment performed in subsequent session.

The Consolidated Standards of Reporting Trials (CONSORT) [17] will be followed to ensure greater transparency and quality of the proposed randomized clinical trial (Fig. 3).

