### Subjects

Thirty primary anterior teeth will be selected in health male and female children with no ethnicity restriction. The teeth must be with diagnosis of dental caries or trauma with pulp envolvement. The children will be recruited at pediatric dentistry of University os Nove de Julho (São Paulo - Brasil). The parents or legal guardian will sign the statement of informed consent. Based on a previous study by Pinheiro et al. [7] for sample size calculation it was considered the standard desviation (2.41) and the diference to be detected in the median of colony forming units per milimiter (CFU/ml) before and after PDT 2.9, with significance level of 5 % and power of 95 %.

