### Microbiological analysis

All samples will be collected with three paper cones, which will be inserted into the root canal before and immediately after treatment and placed into brain heart infusion broth for culturing to allow the determination of the total number of viable bacteria. The samples will be homogenized for 3 minutes in a vortex agitator, followed by dilution in 4.5 ml of peptone water of the order of 10^−6^. Three 25-μl aliquots of the decimal solution will be sewn into Petri dishes with blood agar [7]. The cultures will be incubated for 5 days at 37 °C in an 85 % nitrogen (N_2_), 10 % carbon dioxide (CO_2_) and 5 % hydrogen (H_2_) atmosphere obtained though the use of an anerobiosis generation system to allow the visualization of the total number of viable bacteria in CFU [7].

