### Data organization and statistical analysis

The data will be tabulated and presented in a descriptive and analytical manner. Descriptive statistics will involve the determination of frequency, mean and standard deviation values. The Kolmogorov-Smirnov test will be used to determine the distribution of the data (normal or non-normal). Depending on the distribution, differences between groups regarding mean CFU and percentage reduction in bacteria will be determined using either the *t* test, analysis of variance (ANOVA) or the Mann-Whitney test. The Wilcoxon test will be used for comparisons before and after treatment. *P* values < 0.05 (95 % significance level) will be considered indicative of statistically significant differences. All statistical analyses will be conducted with the aid of the SPSS 21 program (SPSS Inc., Chicago, IL, USA).

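### Only the PDT arm has a saline rinse written in before the second bacterial sample, so the between-arm CFU comparison estimates PDT plus rinse rather than PDT alone

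*Protocol article*

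**What the plan says.** The Protocol article sets out the two procedures as step lists, under Group I (control) and Group II (conventional treatment plus PDT). They match almost word for word up to the end of canal preparation, and both take the first bacterial sample in the same way.

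- **Group I.** Files are used "with irrigation and aspiration with 1 % sodium hypochlorite" and Endo-PTC. The next listed step is "Insertion of 3 sterile paper cones for 30 seconds for second collection of bacterial sample and immediate placement into brain heart infusion broth".
- **Group II.** After the same preparation come the dye-soaked cone and the laser, and then "Root canal irrigated with sterile saline solution and insertion of 3 sterile paper cones for 30 seconds for second collection of bacterial sample".

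The Microbiological analysis section describes sampling for both arms together: "All samples will be collected with three paper cones, which will be inserted into the root canal before and immediately after treatment". It mentions no rinse for either arm.

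The Data organization and statistical analysis section says that "differences between groups regarding mean CFU and percentage reduction in bacteria will be determined". The second sample enters both of those measures. Bacterial count is also the only variable named in the sample size statement (Subjects section).

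**The concern.** If the CFU contrast is to be read as the effect of PDT, the arms should differ only by PDT at the moment the outcome sample is taken. As written, they also differ in whether the canal is rinsed just before the cones go in.

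Two opposing effects are plausible, although the document describes neither:

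- The rinse could wash out loose bacteria and lower the Group II count.
- In Group I, residual hypochlorite could be carried on the cones into the broth and lower the Group I count. The rinse would reduce such carry-over in Group II.

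The rinse follows allocation exactly: every Group II tooth is due to have it and no Group I tooth is listed as having it. Randomisation therefore does not balance it, and no covariate adjustment can separate it from PDT. Using percentage reduction does not cancel it either, because no rinse is listed before the first sample in either arm. Each tooth has a single post-treatment sample, so nothing collected later can recover the missing comparison.

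**Working it through.** **Setting the lists side by side.**

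| Step | Group I | Group II |
|---|---|---|
| First sample | 3 cones, 30 s | 3 cones, 30 s |
| Preparation | hypochlorite + Endo-PTC | hypochlorite + Endo-PTC |
| Dye and laser | no | yes |
| Saline irrigation | none listed | yes |
| Second sample | 3 cones, 30 s | 3 cones, 30 s |

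Two rows differ, not one. The contrast at the second sample is (PDT + rinse) against (neither).

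**The plan's own sample size, to fix a scale.** Inputs from the Subjects section are SD 2.41, difference 2.9, significance level 5% and power 95%. Table 1 gives 15 per group. With the two-sample normal approximation, n per arm = 2 × [SD × (z_alpha + z_power) / difference]².

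- One-sided: 2 × [2.41 × (1.645 + 1.645) / 2.9]² = 14.95, so 15 per arm. This matches.
- Two-sided: 2 × [2.41 × (1.960 + 1.645) / 2.9]² = 17.95, so 18 per arm. This does not match.

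The stated 15 per group is therefore reproduced by a one-sided two-group calculation with SD 2.41. However, the article describes the 2.9 as "the diference to be detected in the median of colony forming units per milimiter (CFU/ml) before and after PDT 2.9" and gives neither a measurement scale nor the sidedness. That is a separate matter; here it only limits how far the next figures can be trusted.

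**What a sampling shift could do (illustration only).** The document gives no size for a rinse effect. Assume a net shift b in the arm difference on the scale where the SD is 2.41, 15 per arm, a two-sided t test at 5% with 28 degrees of freedom, and no PDT effect.

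Standard error of the difference = 2.41 × √(2/15) = 0.880. Non-centrality = b / 0.880. The rejection rate comes from the non-central t distribution.

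| Assumed b | b / 0.880 | False-positive rate |
|---|---|---|
| 0 | 0 | 5.0% |
| 0.25 | 0.28 | 5.9% |
| 0.5 | 0.57 | 8.5% |
| 1.0 | 1.14 | 19.5% |
| 1.5 | 1.70 | 37.7% |

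The shift could also hide a real effect. If the 2.9 is taken, as a further assumption, to be a true between-arm difference and b works against it, power under the same test falls from 88.9% at b = 0 to 82.8%, 74.9%, 55.0% and 33.6% at the four shifts above.

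**The case against.** **The rinse may belong to PDT.** It directly follows the dye and laser, and may serve to close that procedure by clearing dye. On that reading the trial compares PDT as delivered with conventional treatment, which is a legitimate contrast. This stands as a possibility, but the article does not say so, and the stated aim is the effectiveness of PDT, not of PDT with a final rinse. A reader might infer that no CFU difference could be credited to PDT at all. The document does not support that: PDT remains part of the contrast, and what is lost is the ability to separate it from the rinse.

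**The mechanisms come from outside the document, and they oppose each other.** This stands. Group I canals are aspirated as well as irrigated at each file change, so the amount of hypochlorite left is unknown. A reader might infer that the rinse favours PDT; nothing in the article fixes the direction, and the net shift could be small.

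**The shift sizes have no anchor.** This also stands. It would be tempting to express them as shares of the planned effect, but that would set a between-arm shift against a figure described as before versus after PDT on an unstated scale. The rates show sensitivity; they are not estimates.

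**The article is condensed.** Group I lists no rinse, but it does not say that none is done. This has limited force: both lists go down to burs, file sizes and irrigants, and saline is written into only one of them. The difference is stated in the text, though actual chairside practice may be more uniform.

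**The stated aim is clinical and radiographic.** This stands, and it limits the scope of the point.

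**Conclusion.** The asymmetry is in the written procedures and runs exactly along the arms. As specified, the between-arm comparison of CFU and percentage reduction estimates PDT plus a pre-sampling rinse against neither. How much of any difference is due to the rinse, and in which direction, cannot be determined from the document. The false-positive rates of 8.5%, 19.5% and 37.7% rest entirely on assumed shifts of 0.5, 1.0 and 1.5, with SD 2.41 and 15 per arm; at a shift of 0.25 the rate is 5.9%, close to nominal.

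The problem is confined to the microbiological outcome. That outcome matters because it is the one used for sample size and the one named for between-group testing. A reader might infer that the whole trial is compromised. The document does not support that: the success and failure criteria at 1, 3 and 6 months use clinical signs and radiographs, not this sample, so the sampling difference leaves them untouched.

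**What to change.** Reconcile the Group I and Group II step lists so that whatever happens immediately before the second sample is the same in both arms: the same solution (or none), the same volume, and the same time to cone insertion. State that common step in the Microbiological analysis section too. Which step to adopt is for the sponsor to decide; the statistical requirement is only that it be identical.

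For teeth already sampled, record which pre-sampling procedure was used. Keep all teeth in the main CFU analysis and add a sensitivity analysis limited to teeth sampled under the harmonised procedure, stating its lower precision. For example, if 8 teeth per arm qualified (an assumed number), the standard error of the difference would be 2.41 × √(2/8) = 1.205, against 0.880 with 15 per arm.

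If the step is not harmonised, or the rinse is meant to be part of PDT, say so and describe the CFU contrast as PDT plus rinse.

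The cost is about one line of procedure and a short amendment, with no change to the sample size. It should be done promptly: the Trial status section gives recruitment as September to December 2015, and a second sample cannot be retaken once the canal is filled.
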